### Outcomes

#### Primary Outcome

The primary outcome indicator of this study is the proportion of patients achieving EASI50 after 4 weeks of treatment.

The EASI is used to assess the extent and severity of AD. Four body regions are evaluated separately: head and neck, upper extremities, trunk, and lower extremities. For each region, the percentage of affected area is scored on a 7-point scale (0‐6): 0 (0%), 1 (<10%), 2 (10%‐19%), 3 (20%‐49%), 4 (50%‐69%), 5 (70%‐89%), and 6 (90%‐100%). In each region, 4 clinical signs—erythema, edema or papulation, excoriation, and lichenification—are each graded on a 4-point severity scale (0‐3: none, mild, moderate, or severe). The sum of the 4 signs is multiplied by the area score and a region-specific weighting factor reflecting body surface distribution: head and neck (0.1), upper limbs (0.2), trunk (0.3), and lower limbs (0.4). The total EASI score is obtained by summing all 4 regional scores, ranging from 0 to 72, with higher scores indicating more severe disease. On the basis of the EASI score, the skin lesion condition of patients with AD is categorized as mild (0‐7 points), moderate (7‐21 points), or severe (>21 points). EASI is a static assessment completed independently at each visit. Consistent scoring by the same investigator and proper training ensure accuracy and reliability.

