#### Secondary Outcomes

Secondary outcome measures include multiple efficacy and patient-reported outcomes assessed at weeks 0, 1, 2, and 4, specifically the proportions of patients achieving EASI75 (≥75% improvement in EASI score from baseline) and EASI90 (≥90% improvement in EASI score from baseline), the IGA, the Dermatology Life Quality Index (DLQI), BSA, the Pruritus Numeric Rating Scale (PNRS), the Patient-Oriented Eczema Measure (POEM), and changes in TCM syndrome scores from baseline. The complete study protocol, including detailed information on the secondary outcome measures and assessment time points, is presented in Table 3.

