### Data Collection and Management

This study will adopt a standardized data collection and management procedure. All study data will be collected using CRFs completed by dermatologists who have received unified training. The CRFs consist of six sections: (1) demographic characteristics, including age, sex, date of birth, marital status, and so forth; (2) medical history, including disease history, prior surgical treatments, allergy history, and family history of AD; (3) vital signs and physical examination, including height, weight, and BMI; (4) disease severity and treatment efficacy assessments, conducted at baseline (week 0), week 1, week 2, and week 4, including the EASI, IGA, DLQI, BSA, PNRS, POEM, and TCM syndrome scores; (5) laboratory examinations, including pregnancy testing, routine blood tests, routine urinalysis, and assessments of liver and renal function; and (6) safety and medication information, including prior medication use, concomitant medications, and adverse events.

In this study, a database will be established using EpiData (version 3.1; EpiData Association), with input validation rules defined for each variable, including data type, value ranges, and logical checks. Data entry will be performed independently using a double-entry method, followed by consistency checks between the 2 datasets. Any discrepancies will be resolved by referring to the original CRFs until complete agreement is achieved. The finalized database will be converted into SAS datasets, and data validation and logical checks will be conducted using SAS (version 9.4; SAS Institute) [18].

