### Statistical Analysis

Statistical analyses will be performed using SAS (version 9.4). The primary analysis will follow the per-protocol principle, with supportive analyses conducted under the intention-to-treat framework including all randomized patients. Missing data will be handled under the missing-at-random assumption using sequential regression multiple imputation. This study is designed as an equivalence trial, with the primary end point being the proportion of patients achieving EASI50 at week 4. The prespecified equivalence margin (Δ) was set at 15% based on clinical considerations. Equivalence will be assessed using the 2-sided 95% CI approach: the difference in EASI50 response rates between groups will be estimated, and the corresponding 95% CI will be constructed using the chi-square test. Equivalence will be concluded if and only if the entire CI lies within the predefined margin of −15% to +15%. For intergroup comparisons among the 4 treatment groups, an overall test will first be performed. Subsequently, pairwise comparisons will be conducted where appropriate. Between-group comparisons will be performed using the Student *t* test (2-tailed) or Wilcoxon rank-sum test, as appropriate. For multiple pairwise comparisons, Bonferroni correction will be applied to control for type I error. Linear mixed-effects models will be applied for continuous outcomes, and generalized linear mixed models will be used for binary outcomes, with subject-specific random effects to account for within-subject correlation and to appropriately handle missing data. Categorical variables will be expressed as frequencies and percentages and compared using the chi-square test or Fisher exact test. In addition, a dose-response model will be constructed to characterize the dose-response relationship of granules and to explore the formulation conversion between granules and traditional decoction. Except for the equivalence testing described above, a 2-sided *P*<.05 will be considered statistically significant.

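### Continuous secondary outcomes get both t/Wilcoxon tests and mixed models with no main analysis named; the tests cannot adjust for baseline or hospital, and no baseline adjustment is stated for the model.

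*Protocol article*

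**What the plan says.** Three statements in the protocol article's Statistical Analysis section matter here.

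- Between-group comparisons use the Student t test ("2-tailed) or Wilcoxon rank-sum test, as appropriate"). The next sentence reads: "For multiple pairwise comparisons, Bonferroni correction will be applied to control for type I error".
- Directly after that: "Linear mixed-effects models will be applied for continuous outcomes, and generalized linear mixed models will be used for binary outcomes". The models are specified only as "with subject-specific random effects to account for within-subject correlation and to appropriately handle missing data". No fixed effects are listed.
- Missing data are to be multiply imputed under a missing-at-random assumption.

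Secondary Outcomes says the secondary measures are "assessed at weeks 0, 1, 2, and 4". Data Collection and Management confirms that efficacy assessments are "conducted at baseline (week 0), week 1, week 2, and week 4, including the EASI, IGA, DLQI, BSA, PNRS, POEM, and TCM syndrome scores", so a baseline value exists for every scale. Secondary Outcomes also frames one outcome as change: "and changes in TCM syndrome scores from baseline". The Body Surface Area section likewise evaluates BSA relative to baseline. The Randomization section makes hospital the stratification factor. The primary outcome is binary, "the proportion of patients achieving EASI50 after 4 weeks of treatment", and has its own confidence-interval rule.

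**The concern.** Two sets of instructions cover the same five scores: DLQI, BSA, PNRS, POEM and TCM syndrome score. Neither is labelled main, supportive or sensitivity. A t test compares means, a rank-sum test compares ranks, and a mixed model gives model-based contrasts across visits. These can disagree, and nothing says which result is reported as the answer. Bonferroni is written beside the t/Wilcoxon comparisons, so it is also unclear whether it applies to contrasts from the mixed model.

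The second issue is precision. A two-sample t or rank-sum test cannot adjust for baseline score or hospital, although both are recorded for every patient. If such a test decides the result, precision that is already paid for is lost. At stake is how clearly and how precisely the secondary efficacy results can be read. The primary conclusion is not at stake.

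**Working it through.** **Figures in the plan.** The only sample-size figures (94 and 47 before dropout, 100 and 50 after) are for EASI50. None is given for a continuous outcome, so there is no plan figure to reproduce on this point.

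**Inputs.** From the Sample Size section: final arms of 100, 100, 50 and 50, and 5% dropout, which leaves about 95 (100 × 0.95) and 47 (50 × 0.95 = 47.5, rounded down). Assumed, because the documents give neither: the baseline to week-4 correlation r (0.3 to 0.7) and, for the illustration only, a true difference of 0.4 SD.

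**Variance of the treatment contrast,** relative to an unadjusted week-4 comparison (= 1), with equal SDs at both visits:

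- change from baseline, unadjusted: 2(1 − r)
- baseline-adjusted: 1 − r²
- adjusted relative to change score: (1 − r²) / [2(1 − r)] = (1 + r)/2

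Power columns use the effect that an unadjusted week-4 test detects with 80% power at two-sided 0.05 (normal approximation).

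| r | Adjusted, 1 − r² | Reduction vs week-4 test | Change score, 2(1 − r) | Reduction vs change score | Power, adjusted | Power, change score |
|---|---|---|---|---|---|---|
| 0.3 | 0.91 | 9% | 1.40 | 35% | 83.6% | 65.8% |
| 0.5 | 0.75 | 25% | 1.00 | 25% | 89.9% | 80.0% |
| 0.7 | 0.51 | 49% | 0.60 | 15% | 97.5% | 95.1% |

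Equivalently, the unadjusted week-4 test needs 1/(1 − r²) = 1.10, 1.33 or 1.96 times as many patients. The change-score test is worse than the raw week-4 score below r = 0.5 and better above it, and adjustment beats both at each r shown. At r = 0.5 the confidence interval narrows by 13% (√0.75 = 0.866).

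**Illustration with this trial's arm sizes,** d = 0.4 SD and r = 0.5, both assumed:

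Power = Φ( d·√[n₁n₂/(n₁+n₂)] / √(1 − r²) − z ), with r = 0 for the unadjusted week-4 test.

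- 95/95: √47.5 = 6.892 and 0.4 × 6.892 = 2.757. Unadjusted Φ(2.757 − 1.96) = 78.7%; adjusted Φ(2.757/0.866 − 1.96) = 88.9%.
- 95/47: √31.44 = 5.607 and 0.4 × 5.607 = 2.243. Unadjusted 61.1%; adjusted 73.6%.

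These use z = 1.96. The plan also states Bonferroni. If all six pairs of the four arms are tested, alpha is 0.05/6 = 0.0083 and the figures become about 55% to 71% at 95/95, 35% to 48% at 95/47, and 24% to 35% for the two reduced-dose arms against each other (47/47). Absolute power is lower, and the gain from adjustment is of similar size.

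**Hierarchy.** Read side by side, the t/Wilcoxon sentence and the mixed-model sentence both apply to these scores. The article does not say which decides, which visit the t/Wilcoxon tests use, or how a disagreement is resolved.

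**The case against.** The strongest reply is that this is a condensed article and that model details belong in the SAP. For the covariate list this stands. A reader might infer that neither method adjusts for baseline, but the article lists no fixed effects for the mixed model, not even treatment or visit. Baseline could enter as a covariate or as the week-0 response. The text neither includes nor excludes it.

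Three other stronger readings also fail.

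- *The simple tests ignore missing visits.* The section plans multiple imputation, so tests on imputed data would not simply drop them.
- *The simple tests ignore baseline altogether.* TCM score and BSA are framed as change from baseline, and a test on change does use baseline, though less efficiently than adjustment. At r = 0.6 and d = 0.4, both assumed, the gain over a change-score test is about 6 points of power at 95/95 and 9 at 95/47. Over a raw week-4 test it is 14 and 19.
- *The loss falls mainly on the dose-response question.* The section gives dose-response its own model, and nothing says the t/Wilcoxon tests decide it.

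One could also read the simple tests as by-visit comparisons beside a longitudinal model, but the article does not say so. The blinding of the statisticians reduces deliberate selection without settling which result counts.

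What remains does not depend on an unseen SAP. The article itself prescribes two methods for the same outcomes with no order between them, and one of the two cannot adjust for baseline or hospital.

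**Conclusion.** The point holds for the continuous secondary outcomes. Two analyses are prescribed without a hierarchy. The t/Wilcoxon tests cannot adjust for baseline or hospital, and no baseline adjustment is stated for the mixed model. Silence about the model is not evidence that baseline will be left out.

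The direction of the precision loss is certain at any non-zero correlation if an unadjusted week-4 test decides. Its size is not: the reductions of 9% to 49% against a week-4 test, and 35% down to 15% against a change-score test, rest on an assumed r of 0.3 to 0.7, and the power figures at fixed arm sizes also rest on an assumed 0.4 SD effect. No loss has been shown for the mixed model.

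A reader might infer that the main conclusion is threatened. It is not: EASI50 equivalence is decided by its own confidence-interval rule, and no sample-size figure changes. This is a worthwhile improvement that costs no data, not a flaw that endangers the trial.

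**What to change.** For each of DLQI, BSA, PNRS, POEM and TCM syndrome score, name one main analysis: a repeated-measures mixed model of weeks 1, 2 and 4 with arm, visit, arm-by-visit interaction, baseline score and hospital. State that the week-4 contrast decides and that Bonferroni applies to its pairwise contrasts, and give the number of pairs. Keep the t/Wilcoxon comparisons as descriptive or sensitivity analyses only. Other baseline-adjusted models would also serve; what matters is that one is named in advance.

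The cost is a few sentences in the protocol and SAP. It needs no new data, visits or patients. No patient had been recruited when the article was submitted, and analysis is scheduled from March 2027, so the change can be made before any outcome data are analysed.

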### Sample Size

This study is designed as an equivalence clinical trial to compare the traditional decoction and the standard-dose granule of IFN-1, with the primary outcome being the proportion of patients with mild to moderate AD achieving EASI50 after 4 weeks of treatment. EASI50 is defined as the percentage of patients achieving ≥50% improvement in EASI score from baseline, reflecting the treatment’s effectiveness in skin lesion improvement. On the basis of previous studies, the EASI50 rate is expected to be 90% in both the traditional decoction group and the granule group at the standard dose. Setting the equivalence margin at Δ=15%, α=.05 (2-sided), and β=.20, the required sample sizes under a 2:1 allocation are 94 and 47, respectively. Considering a 5% dropout rate, the sample sizes are increased to 100 and 50 for the decoction group and the granule standard-dose group, respectively. To explore the dose-response relationship, we include a two-thirds dose granule group (n=50) and a one-tenth dose granule group (n=50). Additionally, 50 patients are added to the standard-dose granule group to strengthen the robustness of the findings. The final study therefore uses a 4-arm parallel design with an allocation ratio of 2:2:1:1 into traditional decoction (n=100), standard-dose granule (n=100), two-thirds dose granule (n=50), and one-tenth dose granule (n=50).

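### Bonferroni is fixed for the pairwise comparisons although Holm's step-down procedure controls the same error rate and never rejects less often

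*Protocol article*

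**What the plan says.** The Statistical Analysis section of the protocol article judges the primary question on its own: "Equivalence will be assessed using the 2-sided 95% CI approach", with margins of −15% and +15% on the EASI50 difference. The Sample Size section describes the trial as an "equivalence clinical trial to compare the traditional decoction and the standard-dose granule of IFN-1".

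The other group comparisons follow a separate path. "For intergroup comparisons among the 4 treatment groups, an overall test will first be performed". "Subsequently, pairwise comparisons will be conducted where appropriate". "For multiple pairwise comparisons, Bonferroni correction will be applied to control for type I error". The level is given by "Except for the equivalence testing described above, a 2-sided" P value below .05. The pairs are not listed and no divisor is given.

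On the reduced doses, the Sample Size section says: "To explore the dose-response relationship, we include a two-thirds dose granule group (n=50) and a one-tenth dose granule group (n=50"). It gives no power for them. The Statistical Analysis section also plans a separate dose-response model for the granules.

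**The concern.** The article names the multiplicity method, so this is a choice already made and not a detail left open. Single-step Bonferroni holds every comparison to the strictest threshold, even after other comparisons in the family have been rejected. Holm relaxes the threshold after each rejection and still controls the family-wise error rate, with no further assumption on how the tests are correlated. For testing, Bonferroni therefore offers nothing that Holm does not.

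The family may also contain one comparison that does not belong there. For week-4 EASI50, decoction versus standard-dose granule is decided by the equivalence interval. A difference test on the same pair cannot support equivalence, and counting it lowers the threshold for the other pairs.

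What is at stake is some power in the comparisons of reduced with standard granule doses, where the smaller arm has 50 patients.

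**Working it through.** **Inputs.** From the article: four arms of 100/100/50/50, 5% dropout, two-sided 0.05, and "the EASI50 rate is expected to be 90% in both the traditional decoction group and the granule group at the standard dose". Evaluable patients: 100 × 0.95 = 95 and 50 × 0.95 = 47.5, taken as 47. The article gives no response rates for the reduced doses, so those below are assumptions.

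**The plan's own figure.** The only sample size calculation concerns decoction versus standard dose. With 2:1 allocation, the smaller arm needs (1.960 + 0.842)² × 0.90 × 0.10 × (1 + 1/2) / 0.15² = 7.849 × 6 = 47.1 patients and the larger 94.2, which agrees with the stated 47 and 94. It does not cover the dose comparisons.

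**Thresholds.** Four arms give 4 × 3 / 2 = 6 pairs. Bonferroni tests each at 0.05/6 = 0.0083. Holm orders the P values and tests them in turn at 0.05/6, 0.05/5, 0.05/4, 0.05/3, 0.05/2 and 0.05 (0.0083, 0.0100, 0.0125, 0.0167, 0.025, 0.05), stopping at the first failure. Every Holm threshold is at least the Bonferroni one, so each Bonferroni rejection is also a Holm rejection. This holds for any family size above one and for any valid test, including the t and Wilcoxon tests for continuous outcomes.

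**Size of the gain.** 200,000 simulated trials, n = 95/95/47/47, EASI50 compared by pooled two-proportion tests after a significant four-group chi-square test. Rates are in the order decoction, standard, two-thirds, one-tenth.

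| Rates (%) | Comparison | Bonferroni, 6 pairs | Holm, 6 pairs | Holm, 5 pairs (without decoction vs standard) |
|---|---|---|---|---|
| 90/90/80/70 | standard vs two-thirds | 0.181 | 0.215 | 0.249 |
| 90/90/80/70 | standard vs one-tenth | 0.643 | 0.659 | 0.685 |
| 90/90/75/50 | standard vs two-thirds | 0.402 | 0.496 | 0.567 |
| 90/90/75/50 | standard vs one-tenth | 0.996 | 0.997 | 0.998 |

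At 90/90/85/75% the gain from Holm over six pairs is about 1 point for each comparison (0.047 to 0.059, and 0.395 to 0.407).

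**A narrower family.** Holm over only the two standard-versus-reduced granule pairs, without the overall test, gives 0.783 for one-tenth and 0.365 for two-thirds at 90/90/80/70%. With the overall test kept, it gives 0.755 and 0.358.

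**How much is due to the correction at all.** By the pooled normal formula with 95 versus 47, 90% versus 80% has power 0.18 at 0.05/6 and only 0.39 at an unadjusted 0.05. For 90% versus 60%, power is already 0.93 at 0.05/6.

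**The case against.** The strongest objection is that the article never says all six pairs are tested. It leaves the pairs to be chosen as appropriate, and a full analysis plan may fix a smaller family. This stands. A reader might infer that the plan spends its alpha on six pairs and so leaves the dose comparisons with avoidably low power. The documents do not support that, for four reasons:

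- The six-pair family is an inference, and the per-pair level could lie between 0.0083 (six pairs) and 0.025 (two pairs).
- For small differences most of the shortfall comes from 50 patients per reduced-dose arm, as the unadjusted 0.39 shows. For large differences Bonferroni costs little.
- Dose-response is also assigned to a model, and the reduced-dose arms are exploratory with no power claimed.
- Bonferroni is valid, so nothing is stated wrongly about type I error.

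A second objection is that decoction versus reduced-dose pairs are not superfluous. Formulation conversion is a stated aim in both the Statistical Analysis section and the Discussion, so removing those pairs from the tested family is a choice between aims. This also stands. Likewise, the equivalence interval settles decoction versus standard dose only for week-4 EASI50. For the secondary outcomes no equivalence interval is planned, and that pair is not redundant there.

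A third objection is that Bonferroni yields simple simultaneous confidence intervals, which Holm does not. The article plans none for these pairs, so this carries little weight here.

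None of this answers the narrow point: for whatever family of two or more pairs is tested, Holm never rejects less often.

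**Conclusion.** The point holds as a modest efficiency improvement. Bonferroni is valid but is dominated by Holm for these tests. If all six pairs are tested with 95/95/47/47 evaluable, Holm adds about 2 to 3 points at 90/90/80/70% (64% to 66% for one-tenth, 18% to 21% for two-thirds) and about 9 to 10 points for standard versus two-thirds at 90/90/75/50% (40% to 50%). Leaving out the redundant week-4 EASI50 pair as well brings the two-thirds comparison to about 25% and 57% in those scenarios. These sizes rest on assumed reduced-dose rates, on the inferred six-pair family, and on simple two-proportion tests. With fewer pairs the gain changes in size but cannot become a loss. The primary equivalence conclusion does not depend on it.

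**What to change.** In the Statistical Analysis section, replace the Bonferroni correction for pairwise comparisons with Holm's step-down procedure. State that, for week-4 EASI50, decoction versus standard-dose granule is judged by the equivalence confidence interval alone and is not a member of the pairwise family. For the secondary outcomes that pair may stay in.

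As an option, the sponsor could restrict the family to standard-dose granule versus the two-thirds and one-tenth doses. At 90/90/80/70% this would raise power from about 64% to 78% and from about 18% to 36% (76% and 36% if the overall test is kept). The price is that decoction versus reduced-dose comparisons, which bear on formulation conversion, become descriptive, so this is for the sponsor to weigh.

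The main change needs one or two sentences and no patients. The article reports that nobody had been recruited at submission, so it could be prespecified if made before the data are seen.

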### Ethical Considerations

This clinical trial protocol (version 1.0, December 2025) has been approved by the Ethics Committee of Shanghai Skin Disease Hospital (approval 2025‐47) and registered with the International Traditional Medicine Clinical Trial Registry (ITMCTR2026000452). The study will be conducted in strict accordance with the ethical principles outlined in the Declaration of Helsinki and its subsequent amendments. All participants will provide written informed consent prior to enrollment; for participants unable to provide consent themselves, their legal guardians will provide written consent on their behalf.

All signed informed consent forms and collected CRFs will be securely stored in locked facilities and will be accessible only to the study team. All study data will be kept at Shanghai Skin Disease Hospital for 10 years after study completion and will then be destroyed in accordance with applicable regulations.

